## Methods/Design

### Design and Aims

This study will use a randomised and controlled trial to assess the impact of electronic game use on PA in children by:

1) comparing PA and energy expenditure where children have either no electronic games or access to traditional electronic games. We hypothesise that PA and energy expenditure will be reduced when children have access to traditional electronic games.

2) comparing PA and energy expenditure where children have access to either traditional electronic games, new active electronic games and no electronic games. We hypothesise that PA and energy expenditure will be greater with new active electronic games, but still less than no games.

3) examining responses of different children to explore whether the impact of access to electronic games is greater in some children. We hypothesise a stronger effect on children with poor coordination skills, high adiposity, poor social confidence, more positive attitudes to technology and less positive attitudes to PA.

4) examining displacement of sedentary and active leisure activities by electronic games. We hypothesise that all electronic games will displace active non-electronic leisure activities.

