#### Child Self-Perceptions

Harter's Self-Perception Profile for Children [68] will assess self-perceptions across domains of Scholastic Competence, Social Acceptance, Athletic Competence, Physical Appearance and Behavioural Conduct, and it also includes a subscale designed to evaluate global self-worth that assesses self-esteem independent from the competence domains. It has been validated in samples of children from a wide range of cultural backgrounds, including in Australian children and has high levels of internal consistency ranging from .74 to .92 [68].

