#### Attitudes to PA

Attitudes to PA will be assessed using the revised Physical Activity Enjoyment Scale [71]. Internal consistency, test-retest reliability and construct validity has been demonstrated [72-74].

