### Analysis

To examine hypotheses 1 (that PA and energy expenditure will be reduced when children have access to traditional electronic games) and 2 (that PA and energy expenditure will be greater with new active electronic games, but still less than no games) a 4 (baseline and 3 game conditions) × 2 (sexes) repeated measures ANCOVA analysis with pre-specified contrasts will be conducted for each PA and energy expenditure variable. Prior game experience will be used as a covariate. A critical alpha level of 0.01 will be used to balance type 1 and type 2 errors.

To assess hypothesis 3 (that there will be a stronger effect on children with poor coordination skills, high adiposity, poor social confidence, more positive attitudes to technology and less positive attitudes to PA), separate multiple linear regression analyses for both traditional sedentary electronic and new active electronic games will examine the importance of individual characteristics on activity levels (total minutes of overall moderate/vigorous PA). Sex and amount of moderate/vigorous PA at the end of the no game period will be included as baseline covariates for the assessment of the independent effect on PA of; motor competence, adiposity, perceived athletic competence and attitudes to technology. To assess if individual characteristics may impact differently upon the relationship between PA and traditional sedentary electronic versus PA and new active electronic games, beta coefficients and associated 95% confidence intervals, and proportions of total variance explained by these variables, will be compared between the two models.

To assess hypothesis 4 (that all electronic games will displace active non-electronic leisure activities) the impact of the three study conditions on time spent in four outside school activities (reading, watching TV, using computers, playing sports and non-organised physical activity) will be examined using a 3 (no electronic games, traditional electronic games, active electronic games) ×2 (sex) repeated measures MANOVA with weekly minutes in each activity as the dependent variables.

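### The regression for hypothesis 3 leaves out two of its five hypothesised moderators (social confidence and attitudes to PA) and enters one that the hypothesis does not name

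*Protocol article*

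**What the plan says.** In Design and Aims, aim 3 predicts a stronger effect of game access in children with "poor coordination skills, high adiposity, poor social confidence, more positive attitudes to technology and less positive attitudes to PA". That is five characteristics. The Analysis section restates the same five when it introduces the test of hypothesis 3: "stronger effect on children with poor coordination skills, high adiposity, poor social confidence, more positive attitudes to technology and less positive attitudes to PA".

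The same Analysis paragraph then describes one multiple linear regression for traditional games and one for active games, with minutes of moderate to vigorous PA as the outcome. On adjustment it says: "Sex and amount of moderate/vigorous PA at the end of the no game period will be included as baseline covariates". The characteristics whose contribution is to be assessed follow: "independent effect on PA of; motor competence, adiposity, perceived athletic competence and attitudes to technology". That is four, given as a complete list. Coefficients, their 95% confidence intervals and the share of variance explained are then to be compared between the two models.

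The outcome sections describe scales for the constructs missing from that list. Under Attitudes to PA: "Attitudes to PA will be assessed using the revised Physical Activity Enjoyment Scale". Under Child Self-Perceptions, the self-perception profile covers the "domains of Scholastic Competence, Social Acceptance, Athletic Competence, Physical Appearance and Behavioural Conduct", plus global self-worth.

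**The concern.** The paragraph states a five-part hypothesis and then gives a predictor list that does not match it. This is more than the brevity expected of an article, because the predictors are enumerated without any sign that the list is only illustrative. A fuller plan could agree with the hypothesis or with the predictor list, but not with both.

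If the regressions are run as listed, the trial reports nothing on whether social confidence or enjoyment of PA changes the response to games, although the children complete scales that bear on both. It also reports a coefficient for perceived athletic competence that answers no part of the stated hypothesis. The planned comparison between the two game models is affected as well, since adjusted coefficients and variance explained both depend on which predictors are entered. The Background says this exploration is meant to inform the choice of covariates in later epidemiological studies, so the set should be unambiguous.

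**Working it through.** **Step 1: set the lists side by side.**

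| Characteristic | Hypothesis 3 (Design and Aims; restated in Analysis) | Regression predictors (Analysis) | Scale described |
|---|---|---|---|
| Coordination / motor competence | yes | yes | MABC-2 |
| Adiposity | yes | yes | body fat from isotope dilution; waist; BMI z-score |
| Attitudes to technology | yes | yes | flow, ease of use, usefulness |
| Social confidence | yes | **no** | closest: Social Acceptance subscale |
| Attitudes to PA | yes | **no** | Physical Activity Enjoyment Scale |
| Perceived athletic competence | **no** | yes | Athletic Competence subscale |

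Hypothesised and analysed: 3 of 5. Hypothesised but not analysed: 2 of 5. Analysed but not hypothesised: 1 of 4.

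**Step 2: could this be only a difference of wording?** Motor competence and coordination are plainly the same construct. Athletic competence and social confidence are not shown to be: Child Self-Perceptions lists Athletic Competence and Social Acceptance as separate domains. Even if one were accepted for the other, nothing in the predictor list could stand for attitudes to PA.

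**Step 3: the plan's own power figures.** The article gives none for hypothesis 3. Those under Participants concern the contrast between conditions (72 children, difference 15 min, SD 30 min). As a two-sided paired t-test, the noncentrality is 15 / (30/√72) = 4.243 on 71 degrees of freedom. Power is then 0.987 at alpha 0.05 (stated 0.986) and 0.941 at alpha 0.01 (stated 0.943). These figures reproduce closely, and the mismatch does not touch them.

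**Step 4: what adding the two missing terms costs.** Count one term per moderator.

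- Predictors now: 4 characteristics + 2 covariates (sex, no-game PA) = 6.
- After adding two and keeping athletic competence: 6 + 2 = 8.
- Residual degrees of freedom = n − k − 1. At n = 72: 72 − 6 − 1 = 65, falling to 72 − 8 − 1 = 63.
- With the 10% attrition allowance, 72 × 0.9 = 64.8. Taking 64: 64 − 6 − 1 = 57, falling to 64 − 8 − 1 = 55.

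The smallest detectable partial R² for one predictor at 80% power comes from the noncentral F on 1 and n − k − 1 degrees of freedom, with noncentrality n·f² and partial R² = f² / (1 + f²).

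| n | Predictors | Residual df | Partial R², alpha 0.05 | Partial R², alpha 0.01 |
|---|---|---|---|---|
| 72 | 6 | 65 | 0.1010 | 0.1459 |
| 72 | 8 | 63 | 0.1011 | 0.1461 |
| 64 | 6 | 57 | 0.1126 | 0.1622 |
| 64 | 8 | 55 | 0.1127 | 0.1625 |

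For example, at n = 72 with 6 predictors, f² = 0.1123 and 0.1123 / 1.1123 = 0.101. The loss from two extra terms is negligible on this scale.

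**The case against.** The best defence concerns weight rather than fact. Aim 3 is framed as exploration, the power calculation is for the condition contrasts, and no sample size, randomisation or data collection depends on the moderator list. That stands, and it limits the severity.

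Three stronger readings are tempting, and the document does not support them.

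- A reader might infer that hypothesis 3 cannot be answered at all. Coordination, adiposity and attitudes to technology are in the model and can be assessed as planned. Only the five-part statement as a whole goes unanswered.
- A reader might infer that athletic competence has been put in place of social confidence and would be reported as such. Nothing in the article says so. The Background gives perceived athletic competence as an example of a psychosocial influence on children's PA, so it may simply be an additional predictor with a prior rationale.
- A reader might infer that the mismatch leaves a free choice among the six self-perception scores after the results are known. The predictor list names one specific domain in advance. What remains unclear is which of two stated lists governs.

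A further fair point is that the article never equates social confidence with the Social Acceptance subscale. The mapping is plausible but needs the sponsor's confirmation. None of this removes the conflict between the lists.

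**Conclusion.** The inconsistency is real and can be seen within a single paragraph of the Analysis section. Two of the five hypothesised moderators are absent from the stated regressions, and one of the four analysed characteristics is absent from the hypothesis. It is a correction of moderate severity to a secondary analysis; the primary comparison and its power statement stand.

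The finding on attitudes to PA rests on no assumption, since the construct has its own named scale and appears nowhere in the predictor list. The finding on social confidence rests on reading it as distinct from athletic competence, which the separate domains of the profile support. The estimate of negligible cost assumes one term per moderator and modest correlation among the predictors; the article gives no correlations. Strong correlation between, say, the Athletic Competence and Social Acceptance scores would widen the intervals for those terms.

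**What to change.** Make the predictor list in Analysis and the hypothesis in Design and Aims and Analysis agree, before the data are analysed:

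- Add a social confidence measure to both the traditional-game and the active-game regression. The Social Acceptance subscale is the closest one collected; the sponsor should confirm that it is the intended measure.
- Add the Physical Activity Enjoyment Scale score to both regressions.
- Either label perceived athletic competence as an exploratory predictor, or add it to hypothesis 3 in both places where the hypothesis is stated.

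The cost is a change of wording and two more terms in each model. No new data are needed, because the scales are already part of the assessments.

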The proposed mechanism for electronic game exposure to reduce PA is that it displaces more vigorous PA [25]. However there is to date little objective evidence for this, as electronic game use per se has rarely been specifically measured. Cummings et al., in a cross sectional study of 1490 adolescents, found that time spent on video-games was not correlated with time in active leisure for either boys or girls, but did correlate with less reading time [40]. Kautiainen et al. demonstrated that whilst TV viewing and computer use were positively correlated with overweight and obesity in adolescents, time spent playing digital games (video, computer and console games) was not associated with overweight and obesity [34]. Kautiainen et al. suggested that playing digital games may well be less sedentary than has been implied or is indeed simply related to a different lifestyle than viewing TV or using the computer [34]. This is supported by Olds et al. who have documented that certain children can combine high levels of sports participation with high SBM exposure, terming such children "technoactives" [48]. Similarly, Mutanga et al. found some children with high SBM use also had more PA [49].

Rey-Lopez et al. in their review of sedentary behaviour and obesity, conclude that there is a need for methodologically stronger studies to investigate whether (and what type of) sedentary behaviour displaces PA, and how sedentary behaviour influences health outcomes [35]. Our pilot study results suggest that electronic game use displaces some sedentary activities (watching TV, reading books) and some active leisure. We also propose that displacement patterns will be different depending on the nature of the technology (sedentary/active). Whether or not electronic games have an impact on overall PA, their impact on other activities needs to be understood. This project will examine the activities displaced by children when they have access to electronic games.

In summary, there is clearly a need to provide better evidence on this priority health issue [40,25,50]. Specifically whether there is a cause-effect relationship between electronic games and PA needs to be tested experimentally, and the role of potential confounds related to the type of electronic game played and characteristics of the child need to be considered. Finally, the displacement of other leisure activities by electronic game playing needs to be understood.

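### The only test assigned to hypothesis 4 is an omnibus MANOVA over sedentary and active pastimes, so a significant result does not show that active leisure was displaced

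*Protocol article*

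**What the plan says.** Under Design and Aims, aim 4 is broad: "examining displacement of sedentary and active leisure activities by electronic games". The hypothesis that follows it is narrower: "We hypothesise that all electronic games will displace active non-electronic leisure activities". It names one class of activity (active, non-electronic), one direction (displacement) and every type of game.

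The Analysis section repeats the narrow version as the purpose of the test: "To assess hypothesis 4 (that all electronic games will displace active non-electronic leisure activities". The test is a 3 (condition) × 2 (sex) "repeated measures MANOVA with weekly minutes in each activity as the dependent variables". The dependent variables are described as "four outside school activities (reading, watching TV, using computers, playing sports and non-organised physical activity". The article states no contrast, direction, active-leisure composite or significance level for this hypothesis. For hypotheses 1 and 2 the same section specifies a "repeated measures ANCOVA analysis with pre-specified contrasts will be conducted for each PA and energy expenditure variable", at alpha 0.01.

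The Background reports that the pilot suggested "electronic game use displaces some sedentary activities (watching TV, reading books) and some active leisure".

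**The concern.** The null hypothesis for the condition effect in this MANOVA is that no listed activity differs between any of the three conditions. Several departures from that null are not hypothesis 4:

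- television or reading time falls and active leisure is unchanged;
- active leisure rises;
- only one type of game has an effect, or the two game types differ only from each other.

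Three of the listed activities are sedentary, and the pilot points to two of them as displaced. A significant multivariate result is therefore plausible whatever happens to active leisure. The article's Discussion says that displacement of more vigorous activity is assumed but not yet demonstrated, and the stated test cannot isolate that question.

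The number of active outcomes is also unclear. The text counts four activities, but the list reads as five unless sports and non-organised physical activity are merged. If they are merged, only one of the four dependent variables is active.

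**Working it through.** **The plan's own figure.** The only power statement (Participants) concerns physical activity: 72 children, difference 15 min, SD 30 min, power 0.986 at alpha 0.05 and 0.943 at 0.01. A two-sided paired t-test with 30 min as the SD of the difference has noncentrality 15/(30/√72) = 4.24. Its power is 0.987 and 0.941, so the stated figures are reproduced. No power, effect size or SD is given for hypothesis 4.

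**Inputs for the MANOVA.**
- From the article: 72 children with 10% attrition, so 72 × 0.9 = 64.8, taken as n = 65; two sexes; three conditions; k = 4 activities as counted (k = 5 as listed).
- Assumed: television falls by d SDs of the paired difference in both game conditions; nothing else changes; activities are uncorrelated; the two condition differences (each game condition minus none) correlate 0.5; data are normal.
- The top of the range, d = 0.5, equals the standardised effect used for physical activity (15/30). Smaller values are shown because nothing in the article fixes d.

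**Formula.** Each child contributes 2k condition differences. The condition effect is a Hotelling T² test with error df n − 2 = 63, so F has 2k and 63 − 2k + 1 df. The noncentrality is n·d′S⁻¹d with d = (d, d) and S having off-diagonal 0.5, that is n × 2d²/1.5 = 86.67d². For k = 4 the df are 8 and 56, and the critical F is 2.109 (alpha 0.05) or 2.847 (alpha 0.01).

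| Fall in television only (d) | Noncentrality | Rejects, alpha 0.05 | Rejects, alpha 0.01 |
|---|---|---|---|
| 0.2 | 3.47 | 0.18 | 0.06 |
| 0.3 | 7.80 | 0.41 | 0.19 |
| 0.4 | 13.87 | 0.69 | 0.43 |
| 0.5 | 21.67 | 0.90 | 0.72 |

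With k = 5 the last row becomes 0.86 and 0.65.

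**Check by simulation.** At d = 0.5, over 4 or 5 activities, 72 or 64 children, and correlation 0 or −0.2 between activities, the full MANOVA rejected in 0.84 to 1.00 of runs at alpha 0.05 and 0.66 to 0.96 at 0.01. The same test restricted to the active variables stayed near nominal: 0.04 to 0.06 and 0.006 to 0.015.

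**Power for a true effect.** If active leisure, as one of four variables, is the only one to fall, by 0.5 SD in both game conditions, the MANOVA's power is by symmetry the last row of the table: 0.90 and 0.72. One paired contrast of that size with n = 65 has power 0.98 and 0.91. Requiring both contrasts, again with correlation 0.5, gives about 0.96 and 0.85 by simulation. The gain over the MANOVA is therefore about 0.06 at alpha 0.05 and 0.13 at alpha 0.01.

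**The case against.** Four objections carry weight.

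1. **No decision rule is written.** A reader might infer that a fall in television alone would be declared confirmation of hypothesis 4. The article does not say so. It says that the impact of the conditions will be examined by MANOVA, and in ordinary practice activity-level and pairwise results would follow. Those details may stand in a fuller plan that is not shown, and their absence here is not the point. What stands is that the test named for the hypothesis does not match the hypothesis.
2. **Sedentary activities belong in the study.** Aim 4 covers sedentary as well as active leisure, and the diary is meant to give displacement by category. Measuring and jointly analysing television, reading and computer time is legitimate. The mismatch arises only because the Analysis section offers the joint test as the assessment of the narrower hypothesis.
3. **The size is conditional.** It rests on assumed standardised effects. At a fall of 0.2 SD and alpha 0.01, the MANOVA's rejection rate (0.06) is low in absolute terms, though still above nominal. The power advantage of directed contrasts is modest at alpha 0.05.
4. **This is a secondary question.** The primary outcome is accelerometer-measured physical activity, and its analysis has pre-specified contrasts. No primary conclusion and no sample size depends on this MANOVA.

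**Conclusion.** The point holds as a mismatch between a stated hypothesis and its stated test. A significant MANOVA would not show that active leisure was displaced, still less that both game types displaced it. This follows from the null hypothesis of the test and needs no numerical assumption.

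The size does need assumptions. If only television changes, by 0.2 to 0.5 SD, the MANOVA rejects with probability 0.18 to 0.90 at alpha 0.05 and 0.06 to 0.72 at 0.01 (65 children, four uncorrelated activities, correlation 0.5 between the condition differences). The documents do not support the stronger conclusion that the investigators would claim displacement of active leisure on such a result. The point is worth correcting because the remedy is cheap, but it concerns a secondary analysis.

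**What to change.** Separate the hypothesis from the broader aim in the Analysis section.

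- **Hypothesis 4.** Assess it by two pre-specified contrasts on one diary outcome, weekly minutes of active non-electronic leisure (sports plus non-organised physical activity): traditional games versus none, and active games versus none. Require both for the claim about all electronic games. Because both must succeed, alpha need not be split between them. State the alpha level. Summing the two active categories is one reasonable choice; whichever outcome is used should be named in advance.
- **Aim 4.** Keep the joint MANOVA, or report reading, television and computer time as separate displacement estimates with confidence intervals.
- **List of activities.** Reconcile the count of four with the activities named, and say whether sports and non-organised physical activity are one variable or two.

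The cost is a change of wording. The diary already collects the data, and no extra measurement, visit or child is needed.

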## Discussion

Increasing PA is a major health priority internationally due to the associated health burden. It is widely believed that access to electronic games decreases PA in children. Whilst there is considerable research on the impact of TV viewing on PA and obesity, there is little research specific to electronic games. The available evidence suggests electronic games and TV have different associations with PA. Playing electronic games is an important discretionary leisure activity for many children, yet the impact of this on PA has not been tested experimentally. Further, the influence of different game technologies and child characteristics on the impact is not known. Finally, whilst it is assumed playing electronic games displaces more vigorous activities, this has not been demonstrated. As far as we know, this randomised and controlled trial will be the first to experimentally evaluate the impact of access to electronic games in the home environment on children's PA.

